### Eligibility criteria {10}

#### Inclusion criteria

In order to be eligible to participate in this study, a patient must meet all of the following criteria: (1) provide written informed consent prior to initiation of any study procedures; (2) understand and agree to comply with planned study procedures; (3) agree to the collection of oropharyngeal swabs and venous blood per protocol; (4) be male or non-pregnant female adult ≥18 years of age at the time of enrolment; and (5) have laboratory-confirmed SARS-CoV-2 infection as determined by RT-PCR in any specimen no more than 72 h prior to randomization. Both asymptomatic and symptomatic cases (mild/moderate/severe) are eligible for enrolment.

#### Exclusion criteria

An individual who meets any of the following criteria will be excluded from participation in this study:
ALT/AST > 5 times the upper limit of normalStage 4 severe chronic kidney disease or requiring dialysis (i.e. eGFR < 30)Pregnant or breast feedingAnticipated transfer to another facility which is not a study site within 72 hParticipants with known haematological diseases, e.g. G6PD deficiencyParticipants with chronic liver and kidney disease and reaching end-stageParticipants with arrhythmia and chronic heart diseaseParticipants known to have retinal disease or hearing lossParticipants known to have a mental illnessSkin disorders (including rash, dermatitis, psoriasis)Allergy to any study medication (4-aminoquinoline or lopinavir/ritonavir)

#### Lifestyle consideration

Participants will be advised to refrain from alcohol and tobacco use during the period of study.

### Who will take informed consent? {26a}

Informed consent will be taken by trained clinical research assistants (CRAs). Discussions of essential information about the research will include the study’s purpose, duration, experimental procedures, alternatives, risks and benefits, and subjects will have the opportunity to ask questions and have them answered. There will be interpreters at the study sites for potential participants who cannot communicate in English.

### Additional consent provisions for collection and use of participant data and biological specimens {26b}

Potential participants will be asked for consent to collect additional blood by CRAs, the use of residual specimens and samples for secondary research. Extra blood will be drawn for secondary research by CRAs during designated days when study blood samples are obtained.

The stored samples will be labelled with codes to maintain confidentiality. Research with identifiable samples and data may occur as needed; however, subject confidentiality will be maintained as described for this protocol and with HREC approval. Samples designated for secondary research use may be used for understanding the SARS-CoV-2 infection, the immune response to this infection, and the effect of therapeutics on these factors. Samples will not be sold. Although the results of any future research may be patentable or have commercial profit, participants will have no legal or financial interest in any commercial development resulting from any future research.

There are no direct benefits to the participant for extra specimens collected or from the secondary research. No results from secondary research will be entered into the participant’s medical record. Incidental findings will not be shared with the participant, including medically actionable incidental findings, unless required by law. Participants may withdraw permission to use samples for secondary use at any time. They will need to contact the study site and the samples will be removed from the study repository after this study is completed and documentation will be completed that outlines the reason for withdrawal of permission for secondary use of samples.

## Explanation for the choice of comparators {6b}

The comparator for this study is the standard of care at each of the study sites.

The standard supportive for adults with COVID-19 are as stated below (Table 2).

**Table 2 Tab2:** Standard of care for COVID-19 at study sites

Standard supportive therapy	Explanation
Supplemental oxygen therapy immediately to patients with severe acute respiratory infection (SARI) and respiratory distress, hypoxaemia or shock.	• Commence oxygen therapy at 5 L/min and titrate flow rates to reach target SpO_2_ ≥ 90% in non-pregnant adults and SpO_2_ ≥ 92–95% in pregnant patients. • Children with emergency signs, such as breathing difficulty, obstruction or apnea, severe respiratory distress, central cyanosis, shock, coma or convulsions, should receive oxygen therapy during resuscitation to target SpO_2_ ≥ 94%; otherwise, the target SpO_2_ is ≥ 90%. • Wards and outpatients where patients with SARI are cared for are equipped with pulse oximeters, functioning oxygen systems and disposable, single-use, oxygen-delivering interfaces (nasal cannula, simple face mask and mask with reservoir bag). • Contact precautions will be taken when handling contaminated oxygen interfaces of patients with SARS-COV-2 infection.
Conservative fluid management in patients with SARI when there is no evidence of shock.	• Patients with SARI will be treated cautiously with intravenous fluids, because aggressive fluid resuscitation may worsen oxygenation.
Empiric antimicrobials to treat all likely pathogens causing SARI. Antimicrobials (Augmentin 650mg tablets 12hhrly for 24h or Augmentin IV 1g q 24 h) within 1 h of initial patient assessment for patients with evidence of URTI or sepsis.	• The clinicians will administer appropriate empiric antimicrobials within 1 h of identification of sepsis or URTI. • Empiric antibiotic treatment will be based on the clinical diagnosis (community-acquired pneumonia, healthcare-associated pneumonia [if infection was acquired in healthcare setting] or sepsis). Empiric therapy will be de-escalated on the basis of microbiology results and clinical judgment.
• Zinc sulphate tablets 100mg daily • Calcium tablets 300mg daily • Vitamin C tablets 1g daily • Vitamin D tablets 50mcg daily	• Given to all individuals with COVID-19

## Intervention description {11a}

The dose and route of administration of the trial drugs are fixed. The medications will be taken with food. Missed doses for the day will not be made up. All intervention medications will be administered with the standard of care.

### Arm 1

In the chloroquine phosphate arm of the study, participants will receive chloroquine phosphate two 250mg tablets orally twice a day (12h/24h) for 7 days, two hydroxychloroquine placebo tablets orally twice a day (12h/24h) for 7 days and two lopinavir/ritonavir placebo tablets orally twice a day (12h/24h) for 14 days.

### Arm 2

In the hydroxychloroquine arm, participants will receive hydroxychloroquine sulphate two 200mg tablets orally twice a day (12h/24h) for 7 days, two chloroquine placebo tablets orally twice a day (12h/24h) for 7 days and two lopinavir/ritonavir placebo tablets orally twice a day (12h/24h) for 14 days.

### Arm 3

In the lopinavir/ritonavir arm, participants will receive two tablets of lopinavir 200mg/ritonavir 50mg combination tablet orally twice a day (12h/24h) for 14 days, two chloroquine placebo tablets orally twice a day (12h/24h) for 7 days and two hydroxychloroquine placebo tablets orally twice a day (12h/24h) for 7 days.

### Arm 4

In the control arm of the study, participants will receive two chloroquine placebo tablets orally twice a day (12h/24h) for 7 days, two hydroxychloroquine placebo tablets orally twice a day (12h/24h) for 7 days and two lopinavir/ritonavir placebo tablets orally twice a day (12h/24h) for 14 days.

If any of the treatment arms is not available, the placebo for the relevant drug will not be administered to participants in the other arms.

## Criteria for discontinuing or modifying allocated interventions {11b}

If the estimated creatinine clearance decreases by more than ≥ 50% from baseline, the study interventions (oral chloroquine phosphate, hydroxychloroquine sulphate and lopinavir/ritonavir) will not be given. The interventions may be resumed when the estimated creatinine clearance returns to baseline. If the liver function tests (ALT and/or AST) increase to > 2 times upper limits of normal, the dose of chloroquine phosphate, hydroxychloroquine sulphate and lopinavir/ritonavir will not be administered. Dosing may be resumed when the ALT and/or AST returns to baseline. Dosing may be given later the same day. If a day’s dosing is missed, it will not be made up.

If any of the following occur, the dose of chloroquine phosphate or hydroxychloroquine sulphate or lopinavir/ritonavir will be stopped and will not be restarted:
ALT ≥3 × upper limits of normal and bilirubin ≥2 × upper limits of normalALT and/or AST increases to > 5 times upper limits of normal

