2. To evaluate the safety of chloroquine phosphate, hydroxychloroquine sulphate and lopinavir/ritonavir added on to standard therapy compared to standard therapy in the treatment of individuals with laboratory-confirmed COVID-19 2.1 To evaluate the safety of chloroquine phosphate added on to standard therapy compared to standard therapy in the treatment of individuals with laboratory-confirmed COVID-19 2.2 To evaluate the safety of hydroxychloroquine sulphate added on to standard therapy compared to standard therapy in the treatment of individuals with laboratory-confirmed COVID-19 2.3 To evaluate the safety of lopinavir/ritonavir added on to standard therapy compared to standard therapy in the treatment of individuals with laboratory-confirmed COVID-19	1. Cumulative incidence of severe adverse events up to and including day 29 2. Changes in laboratory safety indices assessed on days 1, 8 and 15—haemoglobin concentration, platelet count, white blood cell count, glucose, creatinine, total bilirubin, ALT and AST

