## Efficacy assessments

The schedule of assessments (SOA) in Table 4 outlines the baseline and follow-up assessments that will be done.

**Table 4 Tab4:** Schedule of assessments

Study period	Screening	Baseline	Follow-up days											
Day ± window	−1 or 1	1	2	3	4	5	6	7	8	9	10	11–14	15 ± 2	29 ± 3
1. Eligibility														
Informed consent	X													
Demographics and medical history	X													
Lung auscultation	X													
Chest radiography	X													
Confirm SARS-CoV-2 results^1^	X													
2. Study interventions														
Randomization		X												
Administration of study drugs^2^		X	X	X	X	X	X	X	X	X	X	X		
3. Study procedures														
Vital signs		X	X	X	X	X	X	X	X	X	X	X	X	
Clinical assessment^3^		X	X	X	X	X	X	X	X	X	X	X	X	
Review treatment/management		X	X	X	X	X	X	X	X	X	X	X	X	X
ECG for safety		X		X		X			X			X	X	X
Adverse event evaluation		X	X	X	X	X	X	X	X	X	X	X	X	X
4. Laboratory tests for safety														
Full blood count, liver function tests, creatinine^4^		X							X				X	
Pregnancy test for women of reproductive age	X													
5. SARS-CoV-2 testing														
PCR for SARS-CoV-2		X		X		X			X			X	X	X
6. Sample for future testing														
Oropharyngeal swabs^5^		X							X				X	
Blood/serum^5^		X							X				X	

^1^Time frame for test results: Results of tests done within 72 h of enrolment will be used

^2^Treatment duration: If the patient is still on admission after day 14, standard treatment will continue in all arms of the study while study medications stop on day 7 for chloroquine and hydroxychloroquine and on day 14 for lopinavir/ritonavir

^3^Clinical data to be collected: See the “Efficacy assessments” section for details

^4^Laboratory tests for safety: Blood—haemoglobin, white cell count, platelets, glucose, creatinine, bilirubin, alanine aminotransferase, aspartate aminotransferase

^5^Samples for future research: To be used when additional SARS-CoV-2 tests become available

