## Safety assessments

Study procedures are specified in the SOA. A study physician will be responsible for all trial-related medical decisions.
Physical examination
◦ A symptom-directed (targeted) physical examination will be performed to evaluate for any possible adverse event.Clinical laboratory evaluations
◦ Fasting is not required before collection of laboratory samples.◦ Blood will be collected at the time points indicated in the SOA. Clinical laboratory parameters include WBC, Hb, PLT, Cr, glucose, total bilirubin, AST and ALT.

If a physiologic parameter, e.g. vital signs, or laboratory value is outside of the protocol-specified range (Table 6), then the measurement may be repeated once if, in the judgment of the investigator, the abnormality is the result of an acute, short-term, rapidly reversible condition or was an error. A physiologic parameter may also be repeated if there is a technical problem with the measurement caused by malfunctioning, or an inappropriate measuring device (i.e. inappropriate-sized BP cuff).

**Table 6 Tab6:** Normal reference ranges for vital signs and safety assessments

Parameter	Reference range
Temperature	36.1–37.2°C
Pulse rate	60–100 beats/min
Respiratory rate	12–16 cycles/min
Systolic blood pressure	90–130 mmHg
Diastolic blood pressure	70–90 mmHg
Haemoglobin	12–17.5 g/dl
White blood cell count	4.00–11.0 × 109/l
Platelet count	150,000–450,000/μl
Creatinine	0.5–1.1mg/dl
Random glucose	76–150mg/dl
Total bilirubin	0–1.0mg/dl
ALT	0–40u/l
AST	0–37i.u/l

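### No scheduled liver or renal test falls within chloroquine or hydroxychloroquine dosing to trigger the hold and stop rules, and the liver thresholds overlap with the eligibility limit

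*Protocol article*

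**What the plan says.** **Hold and stop rules ({11b}).** Three sets of rules apply to all three drugs.
- Liver hold: dosing is withheld "If the liver function tests (ALT and/or AST) increase to > 2 times upper limits of normal". Resumption is worded: "Dosing may be resumed when the ALT and/or AST returns to baseline. Dosing may be given later the same day".
- Renal hold: "If the estimated creatinine clearance decreases by more than ≥ 50% from baseline", dosing is withheld, and it may resume once clearance is back at baseline.
- Permanent stops: ALT at or above 3 × ULN together with bilirubin at or above 2 × ULN, or a rise in ALT and/or AST to above 5 × ULN.

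**Laboratory schedule.** Table 3 lists "Changes in laboratory safety indices assessed on days 1, 8 and 15". Table 4 marks full blood count, liver tests and creatinine on the same three days, with a ±2-day window on day 15 and none shown on day 8. The Safety assessments section ties sampling to that table: "Blood will be collected at the time points indicated in the SOA".

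**Dosing periods.** Table 4, footnote 2: "study medications stop on day 7 for chloroquine and hydroxychloroquine and on day 14 for lopinavir/ritonavir". The intervention description {11a} agrees. Both {11a} and {11b} say that missed dosing is not made up, so a hold does not extend a course.

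**Eligibility ({10}).** Patients are excluded for ALT/AST above 5 × ULN and for eGFR below 30. No bilirubin limit is set.

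**The concern.** A hold, stop or resume rule based on a laboratory value needs a result during the dosing that it governs. Here the rules and the schedule appear to have been written separately. For two of the three active drugs the first post-baseline result is due the day after the last dose, so a silent rise in transaminases or fall in renal function would be found only when there is no dosing left to withhold. The provision for giving a dose later the same day presupposes results close together in time, while the schedule supplies one a week.

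The liver thresholds raise a second problem. The level that bars entry is higher than the level that withholds dosing, and resumption is tied to a baseline that may itself be above the hold level. Sites could treat the same participant differently. What is at stake is participant protection and uniform conduct across three centres.

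**Working it through.** The plan states no figure to reproduce here. The check sets the laboratory days against the dosing days, then converts the ULN multiples to values.

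**Step 1. Scheduled results within dosing.** Inputs: laboratory days 1, 8 and 15 ± 2, the last being days 13 to 17 (Table 4); dosing days 1–7 or 1–14 ({11a}; Table 4, footnote 2).

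| Drug | Dosing days | Day 8 | Day 15, nominal | Day 15, window days within dosing | Post-baseline results within dosing (nominal) |
|---|---|---|---|---|---|
| Chloroquine | 1–7 | after last dose | after last dose | none | 0 |
| Hydroxychloroquine | 1–7 | after last dose | after last dose | none | 0 |
| Lopinavir/ritonavir | 1–14 | within dosing | after last dose | 13, 14 | 1 |

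The day-8 draw is 8 − 7 = 1 day after the last chloroquine or hydroxychloroquine dosing day, and no window is shown that would bring it forward. For lopinavir/ritonavir a day-8 result can govern days 8 to 14, which is 14 − 8 + 1 = 7 days. A scheduled retest inside those days requires the day-15 draw to be taken one or two days early.

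Because the design is double-dummy, lopinavir/ritonavir or its placebo is the only study medication still being given from day 8 in any arm. A hold triggered by the day-8 test therefore withholds active drug in Arm 3 only; in Arms 1, 2 and 4 it withholds placebo.

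**Step 2. Liver thresholds in units.** Inputs: upper ends of the Table 6 reference ranges, taken as the ULN (ALT 40, AST 37, total bilirubin 1.0 mg/dl).

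- Hold, above 2 × ULN: ALT 2 × 40 = 80; AST 2 × 37 = 74.
- Exclusion, above 5 × ULN: ALT 5 × 40 = 200; AST 5 × 37 = 185.
- Combined stop: ALT at or above 3 × 40 = 120, with bilirubin at or above 2 × 1.0 = 2.0 mg/dl.

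Two overlaps follow.

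| Baseline value | Barred by a laboratory exclusion in {10}? | Status under {11b} |
|---|---|---|
| ALT above 80 and up to 200, or AST above 74 and up to 185 | No | Already above the hold level; unclear whether the hold applies |
| ALT 120 to 200 with bilirubin 2.0 mg/dl or more | No | Already meets a permanent-stop criterion |

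The hold is worded as an increase to the threshold. Read strictly, a participant who enters above it has not increased to it; read as a ceiling, that participant is withheld from the start. Nor does the resumption rule settle it: "Dosing may be resumed when the ALT and/or AST returns to baseline" would let dosing restart at a value still above the hold level. The combined ALT and bilirubin criterion carries no such wording about an increase, so there the overlap is direct.

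**Step 3. Renal rule.** The hold is a fall to about half the participant's own baseline. Since 0.5 × baseline is always below baseline, nobody admitted under the eGFR limit is in the hold range at entry, so the renal thresholds do not conflict. The renal rule shares the schedule problem in Step 1. Its wording also combines more than with ≥: at a fall of exactly 50% the first says do not hold and the second says hold.

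**The case against.** The best defence is that nothing in {11b} confines the rules to scheduled draws. Adverse events are evaluated on every dosing day, examinations are symptom-directed, and a study physician is responsible for trial-related medical decisions. The adverse event section expects diagnostic tests performed because of an event. Safety assessments also allows for an out-of-range value: "then the measurement may be repeated once if, in the judgment of the investigator", the abnormality is transient or an error. An event-driven test during days 1 to 7 could therefore trigger a hold or stop. This stands, and it limits the point to scheduled data. It does not close the gap: a repeat needs a first result, and an event-driven test needs a clinical event, so a silent laboratory change is not covered.

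A reader might go further in several ways that the protocol does not support.
- *That the rules cannot operate at all.* Not so for lopinavir/ritonavir: the day-8 test can trigger a hold or stop, and the ±2 window permits a later draw within dosing.
- *That the renal hold conflicts with the eGFR exclusion.* It is relative to the participant's own baseline (Step 3).
- *That everyone enrolled between 2 and 5 × ULN is plainly undosable.* The wording about an increase makes this group ambiguous, not contradictory.
- *That participants are allocated before eligibility results are known.* Table 4 shows the tests in the baseline column with randomization, but it gives no order of events within day 1, and screening may itself be on day 1. This is a matter of table clarity.
- *That the intention-to-treat contrast is diluted.* The protocol gives no frequency of raised baseline transaminases, so no size can be attached to this.

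The article format is not a defence: section {31c} calls the document the full protocol, and these are stated figures that do not fit together, not omitted detail.

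**Conclusion.** The point holds in limited form. On scheduled data, the hold and stop rules have 0 post-baseline results to act on during chloroquine and hydroxychloroquine dosing. For lopinavir/ritonavir they have one, with a scheduled retest before dosing ends only if the day-15 draw is taken on day 13 or 14. Separately, the liver eligibility limit admits participants already above the hold level, whose handling is ambiguous, and can admit some who already meet the combined ALT and bilirubin stop.

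This rests on two assumptions: that ULN means the upper end of the Table 6 range, and that courses end on the stated days. The values in units would shift with a different laboratory ULN; the overlap in multiples would not. How many participants are affected cannot be derived from the protocol. The consequence is for participant protection and consistent conduct; no effect on the efficacy estimate is claimed.

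**What to change.** Reconcile {10}, {11b} and Table 4, carrying any change of laboratory days into Table 3:
- Make the laboratory schedule and the hold, stop and resume rules fit the dosing period that each rule governs, so that each can be triggered and, where resumption is allowed, lifted within it.
- Make the liver eligibility limit compatible with the hold and stop thresholds, including bilirubin. State how a participant who enters above the hold level is handled and what baseline means for resumption in that case.
- Correct the comparison in the renal hold so that a fall of exactly 50% has one answer.
- For clarity, show in Table 4 the order of the eligibility laboratory results and randomization on day 1.

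Which passage changes, and to what, is for the clinical team and the medical monitor. The cost is a protocol amendment with ethics committee approval and revised site instructions. Operational cost depends on the side that changes: extra sampling if the schedule moves, little beyond wording and retraining if the rules do.

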## Strategies to improve adherence to interventions {11c}

Participants will be directly observed taking their medications by clinical nurses and CRAs at the study sites to encourage and monitor adherence.

## Relevant concomitant care permitted or prohibited during the trial {11d}

Non-supportive therapy prior to enrolment is permitted. Concomitant therapy for co-morbidities such as hypertension, diabetes, rheumatoid arthritis etc. will be permitted and documented. In addition, the list of participants’ medications will be assessed (from medical history) from at least 30 days prior to enrolment to the 15th day after enrolment.

